## **5. NON-INVESTIGATIONAL PRODUCT**

### **5.1 Name and description of non-investigational product(s)**

Ga-PSMA contains PSMA which binds to the PSMA receptors. This is labelled with Ga through an advanced radiolabelling process.

### **5.2 Summary of findings from non-clinical studies**

Not applicable, the product is used as in usual clinical practice.

### **5.3 Summary of findings from clinical studies**

Not applicable, the product is used as in usual clinical practice.

### **5.4 Summary of known and potential risks and benefits**

### **5.5 Description and justification of route of administration and dosage**

Not applicable, the product is used as in usual clinical practice.

### **5.6 Dosages, dosage modifications and method of administration**

Patients will receive a venous catheter through which  $\pm 100$  MBq of Ga-PSMA is administered (maximum 10mL). The syringe is then flushed with 10mL of saline and removed. No dosage modifications are performed.

### **5.7 Preparation and labelling of Non-Investigational Medicinal Product**

Preparation and labelling is performed according to standard protocol and current GMP-Z guidelines at the NKI-AVL.

### **5.8 Drug accountability**

Not applicable, the product is used as in usual clinical practice.

## 6. METHODS

### 6.1 Study parameters/endpoints

The main study endpoint is to evaluate the PSMA expression variation at 4 week intervals, in terms of uptake difference in prostate and surrounding tissue). The secondary endpoint is to determine the optimal time between  $^{68}\text{Ga}$ -PSMA injection and prostate surgery for future image-guided surgery using Cherenkov Light Imaging. Randomisation, blinding and treatment allocation

No randomization will take place. Scans will be anonymized. Each patient will be assigned a consecutive number. The first and the second scan will be assigned the letter 'A' or 'B', respectively. Only the researchers will be able to see the key, which allocates study numbers to patients. A nuclear medicine physician will assess the anonymized  $^{68}\text{Ga}$ -PSMA PET/CT scans for differences in uptake. This physician is blinded to the order and correspondence between scans.

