Ga-PSMA is an emerging imaging agent that already has been widely proven as a highly effective agent for restaging PCa cells, but also holds enormous potential for initial staging and image guided surgery. During surgery, Ga-PSMA can be probably be used of assessment of the resection margins based on Cerenkov Light emission. This is part of study granted by KWF (grant number 15175). The interval between initial staging and its application in surgical setting, however, ranges from 4 to 6 weeks. Since little is known about the PSMA expression over time without intervention, a study on this is required to verify this. If PSMA expression is equal between both scans, the inclusion and dose determination can be based on the clinical PET/CT scan. In order to validate this, two PET scans will be performed in a test-retest setting in primary prostate patients. Dynamic imaging will be performed in order to get insight into the most ideal scan time. Subsequently this will be used also to establish the ideal timing of surgery after injection.

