### Secondary Objective:

Dynamic imaging will be performed in order to get insight into the most ideal scan time.

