### 3.1 PSMA expression over time

The aim is to obtain preliminary data on variability in PSMA receptor expression by comparing prostate uptake on standard clinical  $^{68}\text{Ga}$ -PSMA PET/CT with additional  $^{68}\text{Ga}$ -PSMA PSMA PET/CT in a 4 week interval.

Primary prostate cancer patients will be included using routine MRI examinations. Based on protocol, a  $^{68}\text{Ga}$ -PSMA PET/CT scan will be advised on high risk prostate cancer patients (cT3, Gleason score >7, PSA >20 ng/mL). These patients will be asked to participate in the study. If they agree to participate, the patients will undergo another  $^{68}\text{Ga}$ -PSMA PET/CT scan within 4 weeks after the routine diagnostic scan. The protocol for the second scan is equal to the standard diagnostic  $^{68}\text{Ga}$ -PSMA PET/CT scan. The PET scan will be acquired at approximately 45 minutes after administration of ~100MBq  $^{68}\text{Ga}$ -PSMA.

In the 5 patients, a dynamic PET/CT-scan (dPET/CT) is acquired up to 40 minutes after administration of the radiopharmaceutical. The dPET/CT scan is performed at one bed position with the prostate in the central field-of-view (FOV). The low-dose CT scan of the same region is made before tracer injection, for attenuation correction and anatomic localization. dPET/CT imaging is started immediately after intravenous injection of 100 MBq  $^{68}\text{Ga}$ -PSMA.

The static PET/CT acquisition is performed directly after the dynamic series. Between the dynamic and static acquisition, the patient is requested to void.

**Table 1.** Division of subgroups in the clinical phase.

| Phase                   | Subgroup   | Administration for PET (MBq) |
|-------------------------|------------|------------------------------|
| 1a – dynamic and static | I. n = 5   | 100                          |
| 1b – static             | II. n = 25 | 100                          |

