### 6.2 Study procedures

Phase 1a: dPET/CT + static PET/CT (n=5)

Phase 1b: static PET (n=25, total=30)

A schedule for one patient is as follows:

First scan  $^{68}\text{Ga}$ -PSMA PET/CT scan as planned (standard clinical care).

Second scan~4 weeks later:  $^{68}\text{Ga}$ -PSMA PET/CT scan (additional for research purposes).

The  $^{68}\text{Ga}$ -PSMA PET/CT scan will be performed according to standard protocol. Patients will receive a venous catheter through which  $\pm 100$  MBq of  $^{68}\text{Ga}$ -PSMA is administered (maximum 10 mL). The catheter is then flushed with 10 ml of saline and removed. After 45 minutes a PET scan is performed directly followed by a low-dose CT scan. When the scans are finished, the patient can leave the hospital. The total procedure (including injection, resting, and scanning) lasts 1.5 hours.

Five patients will undergo a dPET/CT scan as well as a static PET/CT scan. To perform a dPET/CT scan, first a CT scan of the pelvis is made to ensure the location of the prostate. Thereafter, the patient will be injected with  $^{68}\text{Ga}$ -PSMA while lying in the PET/CT scanner. Accordingly, the patient is continuously imaged for 40 minutes. After the scan, the patient is requested to void to better visualize the prostate. Then the standard static PET/CT scan is performed. This study does not interfere with standard clinical care. Both treatment and diagnostic procedures will not be altered or postponed for this study.

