### **7.2 Secondary study parameter(s)**

The  $\text{Bq/mL}_{\text{peak}}$ , derived from the PET scan, and the size, derived from the low-dose CT scan, are determined of each lesion. These values will be compared between both scans.

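### The secondary endpoint (optimal injection-to-surgery time) is not matched by the secondary objective or by section 7.2, and the dynamic data cannot locate an optimum later than the static scan

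*Protocol*

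**What the plan says.** The protocol describes its secondary aim in four ways.

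- Section 6.1: "The secondary endpoint is to determine the optimal time between" injection of the tracer and prostate surgery, for later image-guided surgery. The Summary repeats this endpoint.
- Section 2, Secondary Objective: "Dynamic imaging will be performed in order to get insight into the most ideal scan time". Surgery is not mentioned.
- Section 1, after the same statement about scan time: "Subsequently this will be used also to establish the ideal timing of surgery after injection". The Summary also carries this sentence.
- Section 7.2, Secondary study parameter(s): peak Bq/mL from the PET and size from the low-dose CT are determined for each lesion. Then: "These values will be compared between both scans".

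On data collection, section 3.1 says: "In the 5 patients, a dynamic PET/CT-scan (dPET/CT) is acquired up to 40 minutes after administration of the radiopharmaceutical". Section 6.2 agrees: "Accordingly, the patient is continuously imaged for 40 minutes". Section 3.1 adds: "The static PET/CT acquisition is performed directly after the dynamic series", with voiding in between. The other 25 patients have static scans only, at about 45 minutes after injection.

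**The concern.** There are two linked problems.

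First, the analysis given under the secondary heading does not address the secondary endpoint. A comparison of lesion peak and size between two visits about 4 weeks apart says something about stability over weeks. It says nothing about which minute after injection is best for scanning or for surgery.

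Second, the endpoint is worded as a determination, while the observation window is short and closes with a single static acquisition. If lesion uptake, or its contrast with surrounding tissue, is still rising at that scan, the best observed time is the last observed time, wherever the true optimum lies.

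Followed literally, the study would either leave its secondary endpoint unanswered or report a time set by the end of acquisition. Section 1 intends that result to inform the timing of surgery after injection. The dynamic subgroup also carries extra radiation for this question: by the Summary's figures, 9.3 − 6.3 = 3.0 mSv more than the static group.

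**Working it through.** **Stated figures.** The protocol gives no sample size, precision or decision criterion for the timing endpoint. The 30 patients and 80% power in section 4.4 concern the primary paired comparison. They can be approximately recovered from the protocol's own inputs. With CV 0.6 and correlation 0.80, the SD of the difference is 0.6 × √(2 × 0.20) = 0.379. Section 4.4 states no alpha; with one-sided 0.025, n = (0.379 × (1.960 + 0.842) / (0.30 − 0.10))² = 28.2, so 29. That figure is not in dispute here and has no bearing on timing.

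**Step 1: does the stated analysis answer the stated endpoint?**

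| Place | Quantity of interest | Contrast |
|---|---|---|
| Summary, 6.1 | Best injection-to-surgery time | Times after injection |
| Section 2 | Best scan time | Times after injection |
| 7.2 | Lesion peak, lesion size | First visit against second visit |

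The first two rows need the same kind of data but differ in what they claim. The third row contains no time after injection, no dynamic data and no criterion for an optimum. Neither timing question can be answered from it.

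**Step 2: which times are observed?** In the 5 dynamic patients the observed times are the interval from 0 to 40 minutes and one static point, t_s. The static scan follows directly after the dynamic series and a voiding break. The standard static time is about 45 minutes, so t_s is taken to be near that.

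**Step 3: what can those times identify?** Let f(t) be the quantity to be maximised (uptake, or lesion-to-surrounding-tissue ratio) and t* its true maximiser.

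- If f peaks or levels off before t_s, the window contains the information and the optimum can be described.
- If f is still rising at t_s, the observed maximum is at t_s for every t* at or beyond t_s. The data then cannot separate an optimum at t_s from one at any later time, and the protocol states no extrapolation model.

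The limit is one of coverage. More patients on the same schedule would not remove it. The protocol does not say at which visit the dynamic scan takes place; dynamic scans at both visits would add repeats, but no later times.

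**Step 4: the last point.** Section 6.2 gives better visualisation of the prostate as the reason for voiding. Because the bladder is emptied between the dynamic series and t_s, a step in the lesion-to-surrounding ratio there could come partly from voiding and partly from kinetics. A rise that rests on that point alone is weak evidence that the curve is still climbing.

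**The case against.** The strongest reply is that the study presents itself as preliminary. Section 2 speaks of insight only, section 6.1 refers to future surgery, and no decision for a patient in this study is tied to the timing result. On that view a single over-strong verb, used in 6.1 and the Summary, is the whole problem. This stands in part. It keeps the point at the level of wording and analysis, and the section 2 objective is already close to what the data can support. It does not remove the mismatch, because section 7.2 fits neither version.

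A second reply is that an analysis plan not at hand may describe the analysis of the dynamic data. Silence alone would then be no finding. But the protocol is not silent: under the secondary heading it states an analysis, and that analysis addresses another question. It is also fair to say that lesion peak and size have a use, as supporting measures for the variability objective.

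Two stronger readings are tempting and are not supported.

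- *That the optimal time cannot be determined at all.* The documents give no time-activity data, no criterion for an optimum and no surgical time window. Nothing in them shows that the optimum lies after the static scan; an earlier peak would be seen. Nor does the curve stop short of the routine scan time, since the static scan follows directly.
- *That 5 patients are too few for the endpoint.* A 95% interval from 5 patients has half-width t(0.975, 4 df)/√5 = 2.776/2.236 = 1.24 SD, but this holds for any sample of 5 and contradicts no precision that the protocol claims. Applying the CV (0.6–0.7) and correlation (0.80–0.85) of section 4.4 to two times within one session gives 1.24 × CV × √(2(1 − correlation)), or about ±41% to ±55%. Those inputs were assumed for two scans about 4 weeks apart, and the documents do not support using them within a session.

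**Conclusion.** The point holds in a limited form. The mismatch between the Summary and section 6.1, section 2 and section 7.2 is plain on the text and needs no assumption. The limit on inference is conditional: an optimum later than the static scan cannot be located, and an apparent optimum at the last observed time may reflect only the end of acquisition. That rests on the observation schedule in sections 3.1 and 6.2 and on the absence of any stated extrapolation model.

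The size is qualitative. All times after the single static scan, at roughly 45 minutes, are unobserved in the 5 dynamic patients, and the other 25 contribute no time course. No numerical error is involved, and the primary comparison of 30 patients is untouched. The change is worth making because the protocol otherwise claims to establish a surgical timing that its data may be unable to show.

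**What to change.** Reconcile the Summary and sections 1, 2, 6.1 and 7.2 as follows.

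1. In the Summary and 6.1, restate the secondary endpoint as an exploratory description of early uptake kinetics (lesion uptake, and lesion-to-surrounding-tissue ratio) from 0 to 40 minutes plus the static scan, in 5 patients. Align section 2 with this.
2. In the Summary and section 1, remove the statement that these data will establish the timing of surgery.
3. In 7.2, state the matching analysis: each patient's curve, with the static scan as the last point, marked as acquired after voiding and interpreted with caution for that reason.
4. Add a reporting rule: if uptake or ratio is still rising at the end of observation, report only that the optimum is later than observed.
5. Keep the between-visit comparison of lesion peak and size as supporting measures for the variability objective. Do not present it as the analysis of the timing endpoint, and do not add it to the primary parameter.

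This needs no further patients or scans. It does redefine a stated secondary endpoint, so it is more than an editorial correction, and it leaves the study with a more modest secondary claim. It proposes no time for scanning or surgery.

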## **9. ADMINISTRATIVE ASPECTS, MONITORING AND PUBLICATION**

### **9.1 Handling and storage of data and documents**

The acquired scans are handled and stored following the standard procedure as all scans in the hospital. Additional information about the patient is saved on local computers and anonymised. Patients are coded by a code consisting of a number, PET01, and each PET-scan is randomly designated with either\_A or B. Number will be according to inclusion.. Only the involved researchers have access to the patient code. The encrypted data and the patient encrypted code key will not be stored on the same digital location. Data will be stored on the :S drive, only involved researchers will gain access through this drive. Data will be stored for the next 15 years, as described in the WGBO (Wet op de geneeskundige behandelingsovereenkomst).

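### Sections 6.1 and 9.1 give conflicting scan-labelling rules, and if scans are read under these labels the stated blinding to order and pairing fails

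*Protocol*

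**What the plan says.** Section 6.1 of the protocol covers labelling and blinding in one paragraph:

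- On the patient code: "Each patient will be assigned a consecutive number".
- On the scan letter: "The first and the second scan will be assigned the letter 'A' or 'B', respectively".
- On the key: "Only the researchers will be able to see the key, which allocates study numbers to patients".
- On the reader: a nuclear medicine physician is to assess the anonymised "PET/CT scans for differences in uptake", and "This physician is blinded to the order and correspondence between scans".

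Section 9.1 describes the coding again. "Patients are coded by a code consisting of a number, PET01", numbered by order of inclusion, and "each PET-scan is randomly designated with either" A or B.

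Section 7.1 adds that a nuclear medicine physician determines how many lesions there are and where they lie. Voxel uptake is then obtained in Bq/mL with standard software, and the two scans are compared with a paired t-test. Section 7.2 compares peak uptake and size between scans for each lesion.

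**The concern.** Two things do not fit together. First, 6.1 and 9.1 give different rules for the letter: fixed by scan order in one, random in the other. Second, the blinding statement in 6.1 promises that the reader knows neither order nor pairing, while the codes beside it carry exactly that information.

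The within-patient difference between the two scans is the main result, and the Summary and section 1 explain what hangs on it. If expression is equal on both scans, inclusion and dose determination for image-guided surgery can rest on the clinical scan. The protocol chose blinding as its safeguard for the reading step. A labelling rule that undoes the safeguard is therefore a defect on the protocol's own terms. It is not a detail that could properly be left to an analysis plan.

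**Working it through.** No arithmetic applies, since the point depends on no figure in the protocol. The check sets the two coding rules beside the two parts of the blinding statement.

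| What the label reveals to anyone who sees it | Rule in 6.1 | Rule in 9.1 |
|---|---|---|
| Order of the two scans | Yes: A is first, B is second | No: the letter is random |
| Which two scans belong together | Yes: one number per patient | Yes: one number per patient (PET01 and so on) |
| Identity of the patient | No: key restricted | No: key restricted |

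**Step 1: conflict between sections.** 'Respectively' in 6.1 maps the letters onto first and second in that order. Section 9.1 says "each PET-scan is randomly designated with" one or the other. A letter cannot be both determined by order and random. This conflict holds whatever the reader sees.

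**Step 2: order.** Under 6.1 the letter is the order, so a reader who sees it is not blinded to order. Under 9.1 the letter carries no information about order.

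**Step 3: correspondence.** Both sections give one number to each patient, so both scans of a patient carry it. A reader who sees the number knows the pair under either rule. Adopting 9.1 alone would restore blinding to order but not to correspondence.

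**Step 4: does the key help?** By the wording of 6.1, the key links study numbers to patients. Restricting it hides who the patient is. It does not hide order or pairing, which can be read from the label itself.

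**Step 5: is there another code for the reader?** None is described. In 6.1 the labelling sentences lead directly to the statement that the physician assesses the anonymised scans, so the natural reading is that these are the labels on those scans. The protocol does not say so outright, and steps 2 and 3 bear on the blinding only under that reading.

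**Step 6: the reader's task.** Section 6.1 asks the physician to assess scans for differences in uptake. A difference needs two scans known to form a pair, which is hard to square with blinding to correspondence.

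**Step 7: route to the primary result.** Software supplies the uptake values, so knowing the pair cannot alter a voxel. It can affect which lesions are identified and where they are placed, and therefore which voxels enter the comparison in 7.1 and which lesions enter 7.2.

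**The case against.** The strongest reply is that nothing in the protocol says the reader sees the number or the letter. Section 9.1 concerns data handling and storage, so the codes may serve data management only, and the reader may receive something else. This stands as a limit: the breach of blinding is conditional. It does not remove the conflict between 6.1 and 9.1.

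A second reply is that 'A' or 'B' with 'respectively' is loose wording, and that 9.1, which agrees with the blinding claim, shows what was meant. That is plausible for order. It leaves the shared patient number untouched. The statement in 6.1 that no randomisation takes place does not settle the letter rule either, because it stands under a heading on treatment allocation.

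A third reply is that uptake is measured by software in patients who must have a lesion above 10 mm and PSMA expression on the first scan, so there is limited room for the reader to influence it. This is fair, and it narrows the risk to lesion selection and location.

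A reader might also infer several stronger things that the documents do not support:

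- *That the blinding does not exist.* This needs the assumption that scans are read under these labels, and under 9.1 order would still be hidden.
- *That one physician both identifies the lesions and judges the differences.* Sections 6.1 and 7.1 each refer to a nuclear medicine physician without saying that it is the same person.
- *That the result is biased towards equality.* The stated test is a paired t-test. For a given mean difference, a smaller spread of paired differences makes that test more likely to declare a difference. The net direction depends on what happens to the mean difference as well, which cannot be known from the protocol.
- *That the loss of variability can be quantified.* One could assume that carry-over raises the within-subject correlation above the 0.8 to 0.85 planned in section 4.4 and compute a smaller standard deviation. Nothing in the protocol links labelling to correlation, so any such figure would only restate the assumption.

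**Conclusion.** The point holds in two parts. Without any assumption, 6.1 and 9.1 prescribe incompatible rules for the scan letter. On the assumption that scans are read under the described labels, the 6.1 letter defeats blinding to order, and the shared patient number defeats blinding to correspondence under both sections.

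The labelling applies to all planned study scans (30 patients with two each, 30 × 2 = 60). That is the reach of the rule, not a count of affected readings. The likely consequence is carry-over of lesion identification and location between the scans of a pair, which could make them look more alike. Its size cannot be derived from the documents. The point should be corrected before reading starts, because blinding lost during reading can be recovered only by reading the scans again.

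**What to change.** 1. In 6.1, delete 'respectively' and align the letter rule with the random designation in 9.1.
2. State in both sections which label the reader sees. Give each scan its own random reader ID, unrelated to patient number, scan date or scan order.
3. Have the link between reader IDs and patients held by a researcher who is not the reader. Section 6.1 already restricts the existing key to the researchers, so this adds one condition.
4. Record lesions and uptake for each scan separately. Lock the reads, then match scans and lesions into pairs and compute the differences.
5. Reword the reader's task in 6.1 to match: the physician assesses uptake on each scan, and differences are derived after the lock.

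The cost is an ID list, a few edited sentences, a small amount of extra data handling, and lesion matching as a separate step after the read lock. Scan acquisition and patient procedures do not change.
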